# Prevention of invasive ventilation (PRiVENT)—a prospective, mixed-methods interventional, multicentre study with a parallel comparison group: study protocol

**DOI:** 10.1186/s12913-023-09283-0

**Published:** 2023-03-30

**Keywords:** Invasive mechanical ventilation, Weaning, Weaning failure, Respiratory failure, Medical education and training

## Abstract

**Background:**

Invasive mechanical ventilation (IMV) is a standard therapy for intensive care patients with respiratory failure. With increasing population age and multimorbidity, the number of patients who cannot be weaned from IMV increases, resulting in impaired quality of life and high costs. In addition, human resources are tied up in the care of these patients.

**Methods:**

The PRiVENT intervention is a prospective, mixed-methods interventional, multicentre study with a parallel comparison group selected from insurance claims data of the health insurer Allgemeine Ortskrankenkasse Baden-Württemberg (AOK-BW) conducted in Baden-Württemberg, Germany, over 24 months. Four weaning centres supervise 40 intensive care units (ICUs), that are responsible for patient recruitment. The primary outcome, successful weaning from IMV, will be evaluated using a mixed logistic regression model. Secondary outcomes will be evaluated using mixed regression models.

**Discussion:**

The overall objective of the PRiVENT project is the evaluation of strategies to prevent long-term IMV. Additional objectives aim to improve weaning expertise in and cooperation with the adjacent Intensive Care Units.

**Trial registration:**

This study is registered at ClinicalTrials.gov (NCT05260853).

**Supplementary Information:**

The online version contains supplementary material available at 10.1186/s12913-023-09283-0.

## Background

Medical advances, increased life expectancy [1, 2], and higher morbidity have led to an increase in the number of people who survive prolonged intensive care [3] but still require invasive mechanical ventilation (IMV) thereafter [4]. Whether this is also true for ventilated COVID-19 patients is unclear.

Weaning from IMV is a complex and often lengthy process with the goal of cessation of IMV. According to the Budapest Conference of 2005 [5] and the current German guideline on prolonged weaning [6], different subgroups of weaning can be distinguished ranging from discharge without any further ventilatory support to discharge with invasive ventilation. The perceived quality of life of patients with out-of-hospital continuation of IMV is reduced, especially for elderly patients with chronic lung disease, regardless of whether they are cared for at home or in nursing facilities [7, 8]. Comprehensive care and specialist care in the out-patient setting are also problematic for those invasively ventilated, due to complicated in-hospital visitation [9, 10]. In addition to being dependent on IMV and requiring assistance, long-term IMV also places a burden on the affected family members [11]. Caregivers are left to their own devices, exposed to high levels of stress and as a result are at increased risk of mental illness [12]. Furthermore, health care costs increase due to the need for intensive care [13]. Patients with long-term IMV account for about 10% of intensive care cases in Germany, but tie up about 50% of available resources [14]. Without registries it is difficult to estimate the number of people receiving care outside of hospitals after unsuccessful prolonged weaning. Currently, it must be assumed that about 15,000 people are affected nationwide, with an annual increase of about 10% [11]. There are a number of specialised hospitals that offer units to wean patients of IMV following acute medical care [15]. These so-called weaning centres can be certified by the German Society for Pneumology and Respiratory Medicine (DGP) if they meet the required criteria [16]. Unfortunately, to date these specialised centres treat only a small portion of patients undergoing prolonged weaning. In Germany, up to 85% of patients discharged home with IMV did not have access to a certified weaning centre [13, 17, 18]. Several studies worldwide have shown that 60–80% of patients discharged from non-specialised ICUs with a “non-weanable” classification could still be weaned from IMV after admission to a specialised weaning centre [17–22]. However, this rate decreases when multiple comorbidities are present [18, 23, 24] and the longer the patient was ventilated before transfer to a specialised centre [25]. In addition, in-patient and post-discharge costs increase with the number of ventilator days [26]. Furthermore, the 1-year survival rate of patients with long-term IMV in an out-patient setting is estimated at 62% according to Mifsud et al. [21].

Studies, as PRiVENT, to evaluate interventions in order to reduce long-term IMV are desperately needed from a medical and health economical point of view.

## Methods/design

### Study objectives

The PRiVENT project assesses the effects of an early intervention by weaning specialists on the number of patients requiring out-of-hospital long-term IMV after hospitalisation on an ICU.

Additional objectives are:To reduce the number of ICU patients, who are classified as weaning failures and are not re-admitted to specialised centresTo identify patients requiring specialised weaning therapy in non-specialised ICUs at an early stage to optimise their treatment successImproving the quality of weaning therapy in non-specialised ICUs and, if necessary, transferring high-risk patients in a timely mannerRaising public awareness of weaning therapyEstimating the costs associated with invasive long-term ventilation.Determining the (additional) costs and savings associated with the PRiVENT interventionAssessment of patients’ quality of life during and after invasive long-term ventilation and estimation of the costs and savings related to the impact of the intervention on patients’ quality of life

The project duration is 4 years starting in July 2020. In the first 12 months, the intervention elements were developed, the study protocol was refined, and the participating ICUs were recruited. Furthermore, a small monocentric pilot study was conducted in the preparatory phase to test the individual study elements. The project aims to improve the nursing and medical expertise in the participating ICUs by establishing a weaning consultation with the specialised weaning centres.

In light of the COVID-19 pandemic, patients requiring IMV due to COVID-19 pneumonia should also benefit from the interdisciplinary treatment and care network of the PRiVENT study. Because the prognostic model was developed based on historical health care claims data before the COVID-19 outbreak, prediction of these patients’ risk of long-term IMV was not possible. However, recent studies [27, 28] indicate that patients with acute COVID-19 disease often develop acute kidney injury or cardiovascular events which increases their risk of prolonged weaning. Benito et al. [28] conclude that further studies are needed to determine prognostic factors that might predict weaning success in patients with COVID-19. Altona et al. [29] also suggest that the younger generation, including those without concomitant disease, should be studied more closely. Therefore, patients with COVID-19 pneumonia are generally assigned to the high-risk group and thus participate in the PRiVENT intervention.

In parallel, the PRiVENT process and health economic evaluation will be performed. The process evaluation is described in a separate manuscript in preparation.

### Study design

The PRiVENT study is a prospective, interventional, unblinded, non-randomised multicentre study in an in-patient setting with a parallel comparison group. The study will be conducted with 4 weaning centres and 40 ICUs in Baden-Württemberg, Germany. See Supplement for list of weaning centres and associated ICUs. After 6 months of follow-up, analysis will be compared with a group generated from health claims data of the AOK-BW. The intervention will occur at multiple levels (Fig. 1). At the patient level, high risk patients will receive the PRiVENT intervention which includes expert advice from the weaning centres through newly developed weaning boards and weaning consults. Transfer to the weaning centre will also be possible. The study will end for the patient with discharge from the ICU or from the weaning centre. Other intervention measures include training of health care staff through e-learning opportunities and continuous bedside education. Public relations work is intended to raise awareness of the topic at all levels of society. The intervention was specified according to TIDieR (Template for Intervention Description and Replication), see online Supplement.

**Fig. 1 Fig1:**
[figure not shown]
Logic Model of the PRiVENT intervention

Figure 1 shows the expected working mechanisms of the PRiVENT intervention.

### Outcomes

The primary outcome is defined as the successful weaning from IMV of high-risk patients before discharge from the ICU or from the weaning centre.

Secondary outcomes are:Time from intubation to successful weaning during hospitalisation in hours on the ventilator.Successful weaning for at least 48 consecutive hours in the intervention group, regardless of patient ventilatory status at discharge.Mortality during the in-patient stay.Re-hospitalisation for the same indication within 30 days of discharge.Use of emergency services within 30 days and within 3 months of discharge.No need for IMV 3 months after discharge.Utilisation of rehabilitation services within 3 months of discharge.Re-hospitalisation with IMV within 6 months of discharge.Mortality at 6 and 12 months.

Patients who either die before successful weaning, require continued IMV at hospital discharge, or cannot be discharged within 6 months of starting IMV or by 30th June, 2023, are considered weaning failures. June 30th, 2023, is the last date for which comparison data are available and thus represents a pragmatic threshold to ensure comparability of the intervention and comparison groups.

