#### Comparison group of the intervention study

The comparison group will be matched from AOK-BW health care claims data provided by hospitals in Baden-Württemberg. Because of the necessary processing in AOK-BW the data will be available from late 2019 to late 2023. Only patients ventilated for at least 96 h will be included in the comparison group. Patient data will then be reviewed for the other eligibility criteria and the risk of long-term IMV will be assessed by the prognostic model. Patients admitted to the hospital with acute COVID-19 pneumonia are automatically classified as high-risk. The group of patients used for the primary assessment of the intervention effect will be additionally limited to patients who do not die within 11 days of starting ventilation. This ensures comparability with the intervention group and corresponds to the screening period in the intervention group.

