### Data collection

Data collection in the patient trial group will be conducted via an eCRF by designated ICU staff, weaning centres and the study centre using Redcap (Research Electronic Data Capture). The data of the comparison group is generated from AOK-BW health care claims data, delivered to the aQua Institute (Institute for Applied Quality Promotion and Research in Health Care) and processed there and analysed in the IMBI (Institute of Medical Biometry and Informatics). Data from the e-learning will be evaluated via the Moodle platform, the central learning platform of the University of Heidelberg. Publicity is recorded on the basis of visits/clicks, which is provided by the respective platforms. More detailed information can be found in the Supplement.

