#### Final analysis

The primary outcome, successful weaning before discharge, will be evaluated using a mixed logistic regression model including treatment group, age, gender, acute COVID-19 pneumonia, pre-existing medical conditions via the Charlson Comorbidity Index (continuously) [33], number of ventilation cases of the centre, dependency on ventilatory assistance for at least 3 month within 1 year before admission (with tracheostomy vs without tracheostomy vs none), tracheostomy within 96 h of intubation, extracorporeal support (yes/no), and centre as a random intercept. The analysis population for the primary endpoint will be restricted in order that a possible bias due to the selection effect of the screening window will be minimized. If necessary, missing values will be imputed via a multiple imputation approach. For patients included into the analysis population, intercurrent events (such as death) which would prevent patients’ successful weaning will be counted as weaning failures. A number of sensitivity analysis will be conducted to investigate the impact of the imputation strategy, the 7-day inclusion window, and the choice of covariates.

The analysis of secondary outcomes will include the calculation of appropriate summary measures of the respective empirical distributions (mean, standard deviation, median, interquartile range, minimum and maximum for continuous variables, and absolute and relative frequencies for categorical variables), as well as descriptive *p*-values. In addition, similar mixed models as described for the primary outcome will be used, logistic models for categorical outcomes and linear models for continuous outcomes. Time to event endpoints will be analysed using methods from survival analysis, including Kaplan–Meier estimates, log-rank tests and shared frailty models similar to the primary analysis model. As appropriate, graphical methods will be used to visualise the results. Missing data in secondary outcomes will not be imputed.

In an explorative analysis, clinical data collected within the trial will be used in to identify potentially relevant factors which could help to supplement the developed prognosis model. To this end, an elastic-net approach, as well as decision-tree based models will be used.

A detailed statistical analysis plan will be set up prior to the final analysis. R version 4.0.2 or higher (www.R-project.org) will be used to carry out the analyses.

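### The primary endpoint is tied to two different discharge points, so success and failure are not complements and the two groups could be scored at different points

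*Protocol article*

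**What the plan says.** The Outcomes section gives the primary outcome as "successful weaning from IMV of high-risk patients before discharge from the ICU or from the weaning centre". Later in that section, weaning failures include patients who die before successful weaning, patients who "require continued IMV at hospital discharge", and patients who "cannot be discharged within 6 months of starting IMV or by 30th June, 2023, are considered weaning failures". The failure rule names no group. Its calendar cut-off is said to be one that "represents a pragmatic threshold to ensure comparability of the intervention and comparison groups".

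Three other places bear on the timing:

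- Study design: "The study will end for the patient with discharge from the ICU or from the weaning centre".
- Final analysis: "The primary outcome, successful weaning before discharge, will be evaluated using a mixed logistic regression model". The word discharge has no qualifier here.
- Data sources: for the intervention group, "Data collection in the patient trial group will be conducted via an eCRF by designated ICU staff, weaning centres and the study centre" (Data collection). For the other group, "The comparison group will be matched from AOK-BW health care claims data provided by hospitals in Baden-Württemberg" (Comparison group of the intervention study).

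**The concern.** Leaving the ICU or weaning centre and leaving hospital are separate events. Between them a patient may go to another ward or hospital and change ventilation status. With success fixed at one event and failure at the other, some patients have no unique value on the primary outcome, and two analysts following the article could code them differently.

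The wider risk is that the choice could follow the group. The sentence on when the study ends points the eCRF towards ICU or weaning-centre discharge, whereas hospital-supplied claims point towards the hospital stay. If each group were read where its source most naturally allows, a measurement difference would coincide with treatment group. The covariates listed for the mixed logistic model describe the patient and the centre, so adjusting for them would not remove a difference in how the outcome was read.

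**Working it through.** **1. The two definitions applied to the same patients.** Each patient is discharged alive within both time limits.

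| Status leaving ICU or weaning centre | Status leaving hospital | Meets the success sentence | Meets the failure rule |
|---|---|---|---|
| weaned | weaned | yes | no |
| ventilated | ventilated | no | yes |
| weaned | ventilated | yes | yes |
| ventilated | weaned | no | no |

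Rows 1 and 2 are consistent. Row 3 meets both definitions and row 4 meets neither. The 6-month and 30 June 2023 limits do not help, because that clause does not say which discharge it means. Nor does the unqualified wording under Final analysis.

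**2. The plan's own power figure.** Inputs from Sample size: 1,495 per group, cluster size 25, intra-class correlation 0.1, drop-out 10.6%, failure 20% versus 30%, significance level 5%.

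- Design effect: 1 + (25 − 1) × 0.1 = 3.4.
- Effective size per group: 1,495 / 3.4 = 439.7; × (1 − 0.106) = 393.1, stated as 393.
- Power of a two-sided chi-squared test at 393 per group: 0.901, stated as 90%.

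The figure reproduces. It neither supports nor refutes the point; it supplies a scale for step 3.

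**3. What different scoring points could do (illustration, assumed values).** The article gives no rate of status change between the two discharges.

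*Re-ventilation after ICU or weaning-centre discharge.* Suppose the intervention group is read at ICU or weaning-centre discharge and the comparison group at hospital discharge. Then understatement of intervention failure = share weaned × share of those ventilated again by hospital discharge. The share weaned is 0.70–0.80, the complement of the planned 30% and 20% failure rates.

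| Assumed share ventilated again | Understatement (points) | As a share of the planned 10 points |
|---|---|---|
| 2% | 0.70 × 2 = 1.4 to 0.80 × 2 = 1.6 | 14–16% |
| 5% | 3.5 to 4.0 | 35–40% |
| 8% | 5.6 to 6.4 | 56–64% |

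With no true effect (30% failure in both groups) and 393 per group, shifts of 1.4, 3.5 and 5.6 points would give a significant result with probability of about 0.07, 0.19 and 0.42 instead of 0.05.

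*Weaning after ICU or weaning-centre discharge.* This works in the opposite direction. If it lowers only the comparison group's failure rate, from 30% by 1, 2, 3 or 5 points, power against a true 20% in the intervention group falls from 0.90 to 0.84, 0.75, 0.64 or 0.39.

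Both mechanisms could operate together. Without their rates, neither the sign nor the size of the net effect can be given.

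**The case against.** A reader might infer that the two groups will be scored at different points, and that status at hospital discharge goes unrecorded for intervention patients. The article supports neither statement.

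- No section assigns one discharge point to one group. The failure rule covers patients generally, and its cut-off date was chosen with comparability in mind. The data-source sections say where data come from, not at which moment status is read.
- The sentence on the end of the study follows the description of boards, consults and transfer, and can be read as the end of the intervention. It cannot mean the end of all observation: Study design mentions six months of follow-up, Discharge management provides a telephone interview five to eight weeks after discharge, and the secondary outcomes run to 12 months. The eCRF is also completed by the study centre, with details in a Supplement that is not shown.
- A coherent reading exists. The first sentence may name the endpoint and the later paragraph may give its scoring rule for everyone. The secondary outcome of 48 hours of weaning irrespective of status at discharge suggests that the primary outcome does depend on that status.

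All of this stands against the stronger reading, and it makes the figures in step 3 conditional. It does not remove the contradiction. The coherent reading has to be supplied by the reader, and even then the published outcome sentence names a different discharge from the rule used to score it. This is also not a detail left to the analysis plan: the article states two incompatible anchors, and a later plan can only choose one and overrule the other.

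**Conclusion.** The point holds as a contradiction in the definition of the primary outcome. Taken literally, the plan gives some patients two values and others none. This follows from the text alone and needs no assumption.

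Different scoring by group is a possibility created by the different data sources, not something the article states. The 1.4–6.4 point range rests on three assumptions: that 2–8% of weaned patients are ventilated again by hospital discharge, that 70–80% are weaned, and that only the comparison group is read at hospital discharge. Later weaning would offset or reverse it. The range shows that modest rates of status change could matter against a planned 10-point difference; it does not estimate a bias.

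The wording should be corrected before the outcome is derived, since it concerns the primary comparison and costs little to settle.

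**What to change.** - Name one discharge point and apply it to both groups. Either would remove the contradiction. Hospital discharge at the end of the in-patient episode, linked across transfers, is the natural choice if claims cannot identify ICU discharge.
- Define success and failure as exact complements at that point, so that every patient in the analysis population has one value.
- Keep both existing limits, 6 months from the start of IMV and 30 June 2023. The second is justified by the availability of comparison data. State which discharge they refer to.
- State how ventilation status at that point is derived from the eCRF and from the claims data.
- Align Study design, Outcomes and Final analysis with the chosen wording. In Study design, say whether the sentence on the end of the study means the end of the intervention or the end of outcome recording.

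The cost is mainly a change of wording. If hospital discharge is chosen and status there is not already recorded for intervention patients, one eCRF item is needed, or one question at the existing call five to eight weeks after discharge. The eCRF item is the safer route, because patients who have died by then cannot be interviewed.

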### Recruitment of patients

#### Intervention study experimental group

The experimental group of the intervention study will consist of patients recruited from PRiVENT ICUs. All patients in participating centres on IMV between 96 h and 11 days will be screened for eligibility. This timeframe has been chosen pragmatically to ensure timely assignment of eligible patients to the intervention. Patients who fulfil the eligibility criteria and have given informed consent to participate in the study can be included. As invasively ventilated patients are usually not capable of giving consent, their legal guardian will be informed instead. After undergoing the prognostic model that classifies patients into high- and low-risk groups for long-term IMV, high-risk and all COVID-19 patients will be assigned to the intervention.

Inclusion criteria:

≥ 96 h of invasive ventilationno more than 7 days have passed since the patient completed their 96th hour of invasive ventilation≥ 30 years old≥ 1 comorbidity and/or acute Covid-19 pneumonianot suffering from any neuromuscular disease without weaning potential

No further exclusion criteria.

The time schedule of the patients’ journey can be found in the Supplement.

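### Time from intubation to weaning: the gap between hour 96 and inclusion is event-free in the intervention group only, so without delayed entry the intervention looks slower under no effect

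*Protocol article*

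**What the plan says.** The section Outcomes lists as its first secondary outcome: "Time from intubation to successful weaning during hospitalisation in hours on the ventilator".

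The two groups enter differently. For the intervention group, the recruitment section says "All patients in participating centres on IMV between 96 h and 11 days will be screened for eligibility". The inclusion criteria cap the delay at 7 days after the 96th hour, and consent (usually through a legal guardian) comes before inclusion. For the comparison group, drawn from claims data, it says "Only patients ventilated for at least 96 h will be included in the comparison group". The group used for the primary assessment is "additionally limited to patients who do not die within 11 days of starting ventilation".

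Under Final analysis the general rule is "Time to event endpoints will be analysed using methods from survival analysis, including Kaplan–Meier estimates, log-rank tests and shared frailty models", with the frailty models built like the primary model. The same section recognises the screening window as a source of bias, but for the primary endpoint: it states "The analysis population for the primary endpoint will be restricted in order that a possible bias due to the selection effect of the screening window" is kept small. In the same paragraph, on the primary outcome, it adds: "A number of sensitivity analysis will be conducted to investigate the impact of the imputation strategy, the 7-day inclusion window, and the choice of covariates". Neither delayed entry nor a landmark is mentioned for the time-to-event outcomes.

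**The concern.** An intervention patient included on day 9 was, by construction, still ventilated on days 4 to 9. A similar patient who weaned on day 6, before inclusion, never appears in the intervention group. In the claims data that patient does appear, with an event on day 6. If follow-up is counted from intubation for everyone, the included patient's days 4 to 9 sit in the risk set although no event was possible. This is immortal time (left truncation), and it falls on one group only.

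Under no effect, and with inclusion timing unrelated to weaning prospects, the error runs against the intervention: lower weaning hazard and longer median time on the ventilator. Its size reflects how quickly ICUs include their patients, not what the intervention does. This outcome measures duration of ventilation directly, so a real shortening could be diluted or hidden. Handling death as a competing event does not cure it, because the same empty interval remains in the risk set.

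**Working it through.** **The plan's own figure.** None is given for this outcome. The stated 90% power for the primary outcome reproduces: design effect 1 + (25 − 1) × 0.1 = 3.4; 1,495 / 3.4 = 439.7; × (1 − 0.106) = 393.1; two-sided 5% chi-squared test of 20% vs 30% with 393 per group gives 0.901. It does not bear on this point.

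**Inputs from the article.** Origin at intubation; intervention entry 0 to 7 days after hour 96; comparison entry at hour 96; about 30% weaning failures in the comparison group; follow-up for weaning up to 6 months.

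**Assumptions, not in the article.** Constant weaning and death hazards after hour 96, the same in both groups (no effect); inclusion timing independent of weaning prospects.

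**Closed form.** Let *h* be the total daily hazard of weaning or death, and let the candidate inclusion time be uniform over *a* days after hour 96. Among patients still ventilated at that time, the mean delay is

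m = 1/h − a·e^(−ah) / (1 − e^(−ah)).

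Mean time remaining after inclusion is 1/h, and the proportion eventually weaned is the same in both groups. The ratio of weaning rates, intervention to comparison, counted from hour 96 without delayed entry, is therefore (1/h) / (1/h + m). With a = 7:

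| Weaning / death hazard per day | 1/h (days) | m (days) | Rate ratio |
|---|---|---|---|
| 0.10 / 0.03 | 7.69 | 2.98 | 7.69 / 10.67 = 0.72 |
| 0.07 / 0.025 | 10.53 | 3.11 | 10.53 / 13.64 = 0.77 |
| 0.05 / 0.02 | 14.29 | 3.22 | 14.29 / 17.50 = 0.82 |
| 0.035 / 0.015 | 20.00 | 3.30 | 20.00 / 23.30 = 0.86 |

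Simulation gives the same rate ratios; the corresponding Cox hazard ratios are 0.69, 0.76, 0.81 and 0.85. With a = 4 the rate is understated by 9 to 19%, with a = 2 by 5 to 11%.

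**Second simulation under no effect.** 6,000 patients per group, death hazard 3/7 of the weaning hazard (about 70% wean), deaths censored, cap at 180 days. Standard error of the log hazard ratio is about 0.02. Hazard ratio for weaning, clock from intubation, no delayed entry:

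| Inclusion | Median 7 d from 96 h to weaning | 14 d | 21 d |
|---|---|---|---|
| All at 96 h | 1.04 | 1.01 | 1.00 |
| Uniform, day 4–7 | 0.83 | 0.89 | 0.95 |
| Uniform, day 4–11 | 0.70 | 0.81 | 0.85 |

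The first row shows that the initial 96 h are harmless. In the 14-day case with inclusion over day 4–11, the Kaplan-Meier median from intubation is 21.3 vs 18.0 days. If everyone were included on day 11, the limit of the window, the ratios would be 0.47, 0.64 and 0.75; I do not rest the point on that case.

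**Would the stated day-11 restriction help?** It removes comparison deaths, not comparison weanings. Applied here with inclusion over day 4–11, it gives 0.66, 0.80 and 0.84, slightly worse.

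**Does delayed entry help?** Entering intervention patients at inclusion and comparison patients at hour 96 gives 0.98 to 1.05 across all scenarios, the day-11 case included. A day-11 landmark in both groups gives 0.94 to 1.06.

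**The case against.** The strongest reply is that nothing here is wrong as written. Intubation is a legitimate origin, and the fix keeps it. All three named methods accept start-stop data, the list of methods is open, and a detailed analysis plan is announced for later. On this view, entry to the risk set is an ordinary detail of that plan. What stands is that the article does not forbid delayed entry, so a reader who infers that it prescribes a naive analysis goes too far. What does not stand is that nothing is fixed: the origin, the two unequal entry rules and the methods are all stated, and applied as they read they produce the bias. The authors saw the screening-window problem, yet placed the remedy and the sensitivity analysis with the primary endpoint.

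The details of the primary-endpoint restriction are not given. If it required both groups to be ventilated at day 11 and were extended to this outcome, the bias would go. The article does not say so.

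A reader might also infer that the intervention will be reported as roughly 30% slower, or as harmful. The documents do not support that. The upper end needs inclusion spread over the whole week and fast weaning; the window is an outer limit, and prompt inclusion shrinks the error towards nothing. Nor does the point reach the primary outcome, a binary endpoint that does not use this clock. The secondary outcomes carry descriptive p-values only.

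**Conclusion.** The point holds for this secondary outcome. Only the interval from hour 96 to inclusion matters, and it counts against the intervention when no effect exists. The size cannot be fixed from the article: the illustrative hazard ratio under no effect lies between about 1.0 (all included at 96 h) and about 0.7 (inclusion uniform over 7 days, fast weaning). These figures assume constant hazards and inclusion timing unrelated to weaning prospects. The recovery of a ratio near 1 under delayed entry rests on that second assumption too; if ICUs include patients selectively by prospect of weaning, delayed entry alone does not restore comparability. This should be settled in the analysis plan before the final analysis. It gives no ground for doubting the primary analysis.

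**What to change.** State in the analysis plan that, for time to successful weaning, the origin stays at intubation, intervention patients enter the risk set at their date and time of inclusion, and comparison patients enter at hour 96. Use these left-truncated start-stop data for the Kaplan-Meier curves, the log-rank test and the shared frailty model. Do not compare unadjusted mean or median hours from intubation between the groups.

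Add, as a sensitivity analysis, a common landmark at day 11 with patients still on IMV in both groups. It is not equivalent to delayed entry: it discards every weaning before day 11, and with them any early effect.

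The cost is a few sentences and one entry-time variable; inclusion timing is already needed to check the 7-day criterion. The price is precision early in the intervention curve, where few patients are at risk. The plan should also state the assumption that inclusion timing is unrelated to weaning prospects given the covariates.
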